### Control group

The control group of optical services will receive usual USP visits, while the intervention groups will receive usual USP visits plus a form of BVIs. In the usual USP visit, the customer requests to get their eyes checked for the spectacle prescription, but will otherwise make no other proactive lines. Although a schedule will be developed for each USP to visit sampled OSPs, most visits will be drop-in visits with no prior appointment unless it is a required procedure by the OSP, for example, when USPs have to register online in advance to visit the ophthalmology department of the hospital. The usual USP visit is chosen as the control, because the purpose is to investigate whether patient’s BVI will change practitioner’s behavior and thereby affect the quality of optometry service. It should also be noted that the assessment results in the control group will serve as the cross-sectional survey results of the quality of optometry service.

### Brief verbal interventions

The USP will execute three different forms of BVIs. For each, the USP will deliver exactly the same rendition of the USP cases other than a proactive line before undergoing the eye examination that represents the content of an assigned BVI. The three BVIs are informed by three respective underlying theories: qualification requirement, patient knowledge and social monitoring. In Group A, the USPs will say “I would like to ask for a qualified professional to do the examination/optometry.” or something like that, to create a qualification requirement for better service. In Group B, the USPs will say “I learned from the Internet that subjective refraction is a critical component” to show patients’ knowledge of appropriate procedures. In Group C, the USPs will say “I am a blogger and will share my experience on the Internet” to create a scenario of social monitoring. Except for the first opening statement and BVI, the USPs will not offer any other lines unless prompted by a provider’s question or instruction. They will also provide only standard answers and responses, strictly according to the USP scripts.

BVIs are brief interventions that will be started and concluded with a single USP visit, so we expect few or no cases of discontinuing an allocated intervention. In the case a provider refuses to provide optometry service, the USP will record the reason and visit a replacement provider with similar characteristics.

The intervention will be delivered by highly trained USPs even though they are also real patients. Actually, USP and companion will be trained together, and then always work together. They will be paired according to their free time. The intervention in the study is instant and involves no follow-ups. We will ensure that all participants receive adequate training to ensure the smooth execution of the study. Meanwhile, we will check the quality of USPs’ renditions of their roles and scripts through the voice recordings that the USPs will take with their smartphones during each optical visit. Thus, we expect a high level of adherence to the research protocols, and we will provide feedback to the USPs within 48 h if they do not adhere to the protocols, in order to improve their adherence in further visits.

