**Methods:**

This study will take unannounced standardized patient (USP) with refractive error as the core research tool, both in measurement and intervention. The USP case and the checklist will be developed through a standard protocol and assessed for validity and reliability before its full use. USP will be trained to provide standardized responses during optical visits and receive baseline refraction by the skilled study optometrist who will be recruited within each site. A multi-arm parallel-group randomized trial will be used, with one common control and three intervention groups. The study will be performed in four cities, Guangzhou and three cities in Inner Mongolia, China. A total of 480 optometry service providers (OSPs) will be stratified and randomly selected and divided into four groups. The common control group will receive USP usual visits (without intervention), and three intervention groups will separately receive USP visits with three kinds of BVI on the patient side. A detailed outcome evaluation will include the optometry accuracy, optometry process, patient satisfaction, cost information and service time. Descriptive analysis will be performed for the survey results, and the difference in outcomes between interventions and control providers will be compared and statistically tested using generalized linear models (GLMs).

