### Allocation and blinding

The sample of OSPs will be randomly assigned to the control or the intervention groups with a 1:1:1:1 allocation. The randomization schedule will be computer-generated and stratified by service type (such as hospitals and optical shops). A stratified randomization is used to ensure that the four groups have a similar distribution in type as this characteristic may substantially affect the outcomes.

The allocation of OSPs will be conducted by a statistician otherwise not related to the research. Other than a code for each service provider and the service type, the statistician will have no other identifying information of the sampled participants.

After stratified random sampling, the allocation sequence will be generated by computer, and the randomization for each group will be initiated by the researcher. The USPs will be enrolled by the researcher and assigned randomly to the OSPs in each group. To balance confounding factor of individual USP, each USP will be assigned to four groups for equal visits.

The study subjects (OSPs) will be blinded to their allocation status as we have obtained a waiver for their informed consent. The USPs will not be blinded as they will need to implement BVIs according to the allocation status. The outcome assessors and data analysts will be blinded to reduce subjective analysis.

As no informed consent will be sought, unblinding on the side of OSPs is highly unlikely if possible at all. But if that occurs, a replacement of provider with similar characteristics will be identified for a replacement visit.

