### Baseline refraction

Refraction of each USP will be conducted prior to the launch of the field visits by the skilled optometrist who will be recruited within each setting to conduct individual refraction. For example, the baseline refraction in Guangzhou will be conducted by experienced optometrists from Zhongshan Ophthalmic Center at Sun Yat-Sen University, the state key laboratory of ophthalmology. Each item of the expert prescription will be used as the “optimal spectacle prescription” (Table 1) for a given USP. The tolerance limits (Table 1) are developed from published studies [5, 25–27] and evaluated through experts’ consensus.

**Table 1 Tab1:** Criteria for optimal spectacle prescription

Component of spectacle prescription	Tolerance limits compared with baseline prescription
Spherical power	± 0.50DS
Cylindrical power	± 0.50DC
Cylindrical axis	
(if baseline cylinder power ≤ − 0.50DC) (if baseline >−0.50DC to ≤ − 1.50DC) (if baseline >−1.50DC)	± 7° ±5° ± 2°
Pupil distance	± 2 mm
Corrected visual acuity	± 0.1

DS = diopter sphere, DC = diopter cylinder

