### Outcomes

The primary outcome is optometry accuracy, a dichotomous variable of spectacle prescription. The prescription of a specific USP visit will be considered “accurate” if all of its readings fall within the tolerance limits in Table 1 to the optimal spectacle prescription. Otherwise, they will be judged as inaccurate prescriptions.

We will also assess providers’ adherence to best practices in optometry services as the secondary outcomes, such as the percentage of guideline-recommended procedures performed. We developed the following technical process indicators based on the guideline recommendations [28]: whether practitioners perform subjective optometry, try on adjustments, check old glasses, etc., and whether the operation is standardized and completed. A technical quality assessment checklist will be developed, and the USP will complete this checklist right after each optical visit. In addition to those technical processes of optometry, we will also evaluate patient experience, cost and service time. The patient-centered eye care in optometry or ophthalmology will be assessed with a revised patient perspective patient-centeredness (PPPC-R) rating scale by USP [29, 30]. Table 2 summarizes all outcomes to be collected.

**Table 2 Tab2:** Outcomes and their definitions

Name	Definition	Nature	How it is assessed	By whom
optometry accuracy	whether it is optimally prescribed for spectacle	primary outcome	spectacle prescription	USP and companion
completion of process items	the percentage of recommended procedures performed	secondary outcome	quality checklist	USP and companion
patient experience score	whether it is patient-centered	secondary outcome	PPPC-R rating scale	USP
cost	optometry fees, prices of recommended lenses and frames	secondary outcome	data collection form	USP and companion
service time	optometry time and waiting time	secondary outcome	data collection form	USP and companion

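### USPs know their arm and their refraction answers feed the primary outcome, but the protocol sets no rule for genuine perceptual replies, states no masking of the reference prescription, and is inconsistent on who assesses accuracy

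*Protocol article*

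**What the plan says.** **Masking.** Allocation and blinding states: "The USPs will not be blinded as they will need to implement BVIs according to the allocation status". The same section says that outcome assessors and data analysts will be blinded, and that each USP makes equal numbers of visits in the four groups.

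**Answers during the visit.** Brief verbal interventions states: "They will also provide only standard answers and responses, strictly according to the USP scripts". The sentence before it says that, apart from the opening statement and the BVI, USPs volunteer no lines unless the provider prompts them. The abstract has the same idea: "USP will be trained to provide standardized responses during optical visits and receive baseline refraction". Brief verbal interventions also says: "The intervention will be delivered by highly trained USPs even though they are also real patients".

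**Reference.** Baseline refraction states: "Refraction of each USP will be conducted prior to the launch of the field visits by the skilled optometrist". Role of implementation adds that the study optometrist develops the reference and helps to train the USPs.

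**Primary outcome.** Under Outcomes, a prescription is accurate "if all of its readings fall within the tolerance limits in Table 1 to the optimal spectacle prescription". Table 1 lists sphere, cylinder, axis, pupil distance and "Corrected visual acuity" (limit ±0.1). The process items in Outcomes include "whether practitioners perform subjective optometry, try on adjustments, check old glasses". In Table 2, the column for who assesses optometry accuracy names the USP and companion.

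**The concern.** The primary outcome is meant to measure the provider, but part of it is produced by the patient. Corrected acuity is a patient response. Where a provider does subjective refraction, sphere, cylinder and axis also depend on what the patient reports as clearer. Every component must pass, so a change in one reading can turn an accurate prescription into an inaccurate one, or the reverse.

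The person giving those answers knows the arm. Someone who answers more carefully in BVI visits, even without meaning to, would raise accuracy in those arms. The analysis would read this as a BVI effect on the provider. A blinded scorer cannot undo it, because it happens before the prescription exists. The Background says that differences between providers can be put down to the BVI line alone. That holds only if the USP answers refraction questions the same way in every arm.

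**Working it through.** **1. Do USP answers enter the outcome?** Yes, for some components.

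| Table 1 component | Depends on USP answers? |
|---|---|
| Corrected visual acuity | Yes, whenever it is measured |
| Sphere, cylinder, axis | Yes, where subjective refraction is done; little where the provider relies on autorefraction alone |
| Pupil distance | No |

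**2. Does a stated safeguard cover one USP answering differently by arm?**

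- *Equal visits by each USP in all four groups* balance differences between USPs. They do not balance a within-USP difference between arms, and they expose every USP to every condition.
- *Voice recordings* show what was said and whether the script was followed. They cannot show whether a reply about clarity was true.
- *Blinded assessors* act after the prescription is written. Table 2 also gives the assessment to two people who know the arm.
- *The scripted-answer rule*, read literally, covers perceptual replies and leaves no room for a true one. If it is meant only for conversation, no rule for perceptual replies is stated.

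**3. Illustration of size.** The protocol gives no figure for this point, so the shift *b* below is an assumption. The other inputs come from Sample size calculation: control accuracy 0.441, 120 per arm, and α = 0.05/3 per comparison.

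The plan's own sample size is reproduced first. The unpooled one-sided formula gives n = (2.128 + 1.282)² × (0.441×0.559 + 0.661×0.339)/0.22² = 113.03, so 114 per arm and 4 × 114 = 456. Then 456/0.95 = 480, or 120 per arm.

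Next, suppose there is no true provider effect and answering alone raises accuracy in one BVI arm from p = 0.441 to q = 0.441 + b. With m = (p + q)/2:

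- SE₀ = √[2m(1−m)/120]
- SE₁ = √[(p(1−p) + q(1−q))/120]
- two-sided rejection probability = Φ[(b − 2.394·SE₀)/SE₁] + Φ[(−b − 2.394·SE₀)/SE₁]

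For b = 0.10: m = 0.491, SE₀ = 0.0645, SE₁ = 0.0642. The first term is Φ(−0.85) ≈ 0.198 and the second is negligible.

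| Assumed shift b (points) | False-positive rate at two-sided α = 0.0167 |
|---|---|
| 0 | 1.67% |
| 2 | 2.2% |
| 5 | 5.3% |
| 7.5 | 10.9% |
| 10 | 19.8% |
| 15 | 47.2% |

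A larger trial does not help. The shift stays the same while the standard error shrinks, so the false-positive rate rises.

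**The case against.** The strongest reply is that the scripting sentence is about conversation. It follows a sentence on when USPs may speak. The protocol recruits real patients with real refractive error and excludes people whose prescription may vary, which would make little sense if refraction answers were pre-written. This largely stands. A reader might infer that USPs recite scripted answers to lens comparisons; the text does not say so. What remains is that the rule has no exception, so it should be narrowed.

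Second, strictly standard answers would be the same in every arm and could not by themselves favour one. Drift towards a known target in all arms would raise control accuracy too. This also stands: only answering that differs by arm biases the contrast, and the protocol asks for the same rendition apart from the BVI line. But that instruction cannot be verified for perceptual replies.

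Third, a reader might infer that USPs know their reference prescription, because they are refracted before fieldwork and the study optometrist helps to train them. The documents do not say it is disclosed. They only state no safeguard, and a condensed article may leave this to the full protocol or training manual. The point does not depend on it, since an unmasked USP can answer with more or less care by arm without knowing the target.

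Fourth, a reader might count extra subjective refraction in Group B as bias, because that group's line draws attention to it. More subjective refraction is the provider behaviour the line is meant to prompt, so it is an intended effect. Only differential answering within it would be bias.

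Finally, withholding the reference has limited value, because USPs ask for a prescription at every visit and so see repeated estimates of their own refraction. That is fair. The measure reduces the risk but does not remove it.

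**Conclusion.** The point holds in a limited form. The text establishes that USPs know the arm, that their answers feed an all-components primary outcome, that the answer rule has no exception for perceptual replies, and that Table 2 conflicts with the stated blinding of assessors. The safeguards described do not address one USP answering differently by arm.

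The documents do not establish that such answering occurs, in which direction, or how large it is. The 2 to 15 point shifts are assumptions, and the resulting rates (2.2% to 47.2% per comparison, against 1.67%) show only what a bias of that size would do. They rest on the protocol's 44.1% control accuracy, 120 visits per arm, a two-sided test and a normal approximation. The scope is smaller where providers rely on autorefraction.

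This should be corrected before visits begin, because prescriptions shaped by arm-dependent answers cannot be repaired in the analysis.

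**What to change.** 1. **Brief verbal interventions:** limit the script to the opening line, the BVI, history and verbal requests. State that all acuity and refraction answers are the USP's genuine perception, given in the same way in every arm, and train to that rule.
2. **Baseline refraction:** state that the expert prescription and the accuracy result of any visit are withheld from USPs and companions until fieldwork ends.
3. **Table 2:** have the USP and companion only capture the prescription. Comparison with baseline is done centrally by assessors blinded to arm, which brings the table into line with Allocation and blinding.
4. **Background and Discussion:** acknowledge residual bias from the unavoidable unmasking of USPs as a limitation, and soften the claim that differences are due to the BVI line alone.

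The cost is protocol and training wording, plus a central comparison step. The small downside is that USPs learn their expert result late. These changes reduce the risk but cannot remove it, because whoever delivers the intervention must know the arm.

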### Statistical analysis plan

Data will be analyzed on an intention-to-treat (ITT) basis to compare primary and secondary outcomes in the originally assigned groups. Baseline characteristics for each group will be descriptively presented using mean (standard deviation, SD) or median (interquartile range, IQR) for continuous variables depending on the distribution, and frequency (percent) for categorical variables.

Primary outcome (optometry accuracy) and secondary outcomes will be analysed using generalized linear models (GLMs). Binomial distribution and identity link function will be used for binary outcomes, Poisson distribution and identity link function will be used for count outcomes, and normal distribution and identity link function will be used for continuous outcomes. Effects (risk differences for binary and count outcomes, and mean differences for continuous outcomes) with corresponding two-sided 95% confidence intervals will be estimated. Missing data will be imputed using multiple imputation in the GLMs.

Sensitivity analysis will be performed by covariate-adjusted analysis using GLMs with baseline characteristics as covariates. Cost-effectiveness analyses will be performed, and cost-effectiveness ratios will be calculated using bootstrapping techniques. Statistical significance will be considered to be present when the P value is < 0.05. Subgroup analyses will be performed, based on the type of service (hospitals and optical shops) and types of practitioners (such as licensed vs. unlicensed practitioners). IBM SPSS (version 20) and SAS (version 9.4, SAS Institute) will be used for all statistical analyses.

Subgroup analyses will be performed, based on type of service (hospitals and optical shops) and types of practitioners (such as licensed vs. unlicensed practitioners).

We expect the number of withdrawals to be low because the intervention is delivered by the USP and the service provider will receive the intervention passively. Additionally, the intervention will be conducted over a brief period of one USP visit thus without post-visit follow-ups. All data will be entered into the REDCap system immediately after the visit. Thus, we expect to have minimum (if any) missing data. A maximum dropout and/or missing data of 5% is considered in our sample size calculation. We will analyze the data according to the ITT principle.

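### Replacing randomised providers after a refusal or a detection conflicts with the promised intention-to-treat analysis, and refusals that a BVI provokes drop out of the result

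*Protocol article*

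**What the plan says.** The unit of randomisation is the provider (Protocol article, Allocation and blinding): "The sample of OSPs will be randomly assigned to the control or the intervention groups with a 1:1:1:1 allocation." The Sample size calculation section ties each OSP to a single USP visit.

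The arms differ only in what the USP says. Under Brief verbal interventions the rendition is identical "other than a proactive line before undergoing the eye examination that represents the content of an assigned BVI." The control visit has no such line.

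Two replacement rules act after randomisation:
- Refusal (Brief verbal interventions): "In the case a provider refuses to provide optometry service, the USP will record the reason and visit a replacement provider with similar characteristics."
- Detection of the USP by the provider (Allocation and blinding): "But if that occurs, a replacement of provider with similar characteristics will be identified for a replacement visit."

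The Statistical analysis plan section says: "Data will be analyzed on an intention-to-treat (ITT) basis to compare primary and secondary outcomes in the originally assigned groups." It repeats the ITT principle at its end and plans multiple imputation for missing data.

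Refusal is not among the outcomes in Table 2; only its reason is recorded. The Outcomes section defines accuracy on the prescription and has no rule for a visit that ends without one.

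**The concern.** An intention-to-treat comparison is protected because every randomised unit stays where chance put it. Here a unit can be exchanged because of something that happened after allocation, and that event can depend on the arm. Group A asks for a qualified professional, while the eligibility criteria admit unlicensed staff. Group C announces a blogger who will post online. Either line could prompt a provider to decline or to become suspicious, and the control visit gives no such prompt.

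Two things are at stake. First, if refusal or detection differs by arm, each arm is partly selected on willingness to serve, and the comparison no longer rests on randomisation alone. Second, the Discussion presents BVIs as something that patients could use themselves. For such a patient, being turned away because of the line is a consequence of using it, and replacement takes that consequence out of the result.

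The same selection touches two other aims. The consent waiver is justified by the wish to avoid provider self-selection, and the control arm also serves as the cross-sectional quality survey.

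**Working it through.** **1. The plan's own figure.** Inputs from Sample size calculation: 0.441 in control, 0.661 with BVI, alpha 0.05/3, power 0.90. The unpooled normal formula, one-sided, gives

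n = (2.128 + 1.282)² × (0.441×0.559 + 0.661×0.339) / 0.22² = 113.03, so 114 per arm. 4 × 114 = 456, and 456/0.95 = 480.

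The stated figures reproduce exactly, so this point does not rest on a wrong sample size. The article does not state the sidedness; one-sided is what reproduces 456.

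**2. The rules side by side.** Suppose OSP X is allocated to Group C, refuses, and OSP Y is visited instead.
- If Y stands in for X, the analysed group is not the one randomised.
- If X stays in, it needs an outcome, and none is defined. Multiple imputation would fill in a prescription that was never issued. Y is then an extra unit.

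On either reading the two replacement rules and the ITT statement do not describe the same set of providers.

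**3. Possible shift under replacement.** Assumptions, since the article gives no rates: the BVI has no effect on accuracy; a share r refuses in one BVI arm and nobody refuses in control; refusers would have been accurate with probability a; substitutes come from the same population and are willing. Then

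accuracy in the BVI arm = (0.441 - r·a)/(1 - r), and the shift is this minus 0.441.

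| r | a | BVI arm | Shift (points) |
|---|---|---|---|
| 5% | 0 | 0.441/0.95 = 0.464 | +2.3 |
| 5% | 1 | 0.391/0.95 = 0.412 | -2.9 |
| 10% | 0 | 0.441/0.90 = 0.490 | +4.9 |
| 10% | 0.25 | 0.416/0.90 = 0.462 | +2.1 |
| 10% | 0.441 | 0.3969/0.90 = 0.441 | 0 |
| 10% | 0.60 | 0.381/0.90 = 0.423 | -1.8 |

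The sign depends entirely on a. For scale, the design difference is 22 points, and the standard error of a two-arm difference at 120 per arm is √(2×0.441×0.559/120) = 0.064, or 6.4 points.

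**4. What replacement hides.** If refusal is unrelated to accuracy, the shift is zero. Patients in the BVI arm still lose service: counting refusal as not accurate gives 0.441×(1 - r) - 0.441, which is -2.2 points at r = 5% and -4.4 at r = 10%.

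**5. Effect on power of counting refusals as not accurate.** Design rates, 120 per arm, the formula from step 1, refusals in the BVI arm only:

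| Refusal | Difference | Power | n per arm for 90% |
|---|---|---|---|
| 0% | 0.220 | 91.7% | 114 |
| 2% | 0.661×0.98 - 0.441 = 0.207 | 87.7% | 130 |
| 5% | 0.661×0.95 - 0.441 = 0.187 | 79.6% | 160 |
| 10% | 0.661×0.90 - 0.441 = 0.154 | 61.3% | 240 |

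Two-sided, the same unpooled formula gives 86.8%, 81.4%, 71.3% and 50.8%.

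**The case against.** **Exclusion is inferred.** No sentence says that a replaced OSP leaves the analysis, and a fuller protocol or SAP may define the analysis set. That is true. But the replacement rule is already fixed for the field, and an SAP could reconcile it with ITT only by giving the replaced OSP an outcome. The contradiction in this document stands.

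**Events may be rare.** The article expects discontinuation to be very uncommon and unblinding to be very unlikely, and it allows 5% for all dropout and missing data. This stands, and it limits the likely size.

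**The refusal may come before the line.** The opening request comes first, and a refusal at that point cannot be caused by the BVI. This also stands. The article does not separate the two cases.

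**Accuracy among services delivered is a legitimate question.** It is, and the Control group section describes the aim as changing practitioner behaviour. It is not an ITT question, however, and the plan promises ITT.

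A reader might infer two stronger things. One is that an arm with more refusals must look better than it is; this needs refusers to be less accurate than average, which nothing in the documents supports. The other is that the unblinded USP picks the substitute. The article says "The USPs will not be blinded as they will need to implement BVIs according to the allocation status" and that the USP visits the replacement, but it does not say who selects it.

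**Conclusion.** The point holds as a contradiction between the two replacement rules and the ITT statement, and it affects the primary comparison at any refusal rate. Bias is possible but not demonstrated, and it can go either way. With an assumed 5% refusal in one BVI arm only, the spurious difference lies between -2.9 and +2.3 points at the extremes. With 10%, plausible values of refusers' accuracy give +4.9 (none accurate), +2.1 (25%) or -1.8 (60%). These sizes rest on assumed rates, no refusals in control and no true effect. If events are as rare as the article expects, the numerical effect is small against the 22 points designed for.

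A reader might also infer that detection should count as a failure of the strategy, as refusal does. The documents do not support this: a genuine patient cannot be unmasked as a researcher, and a detected visit can still yield a correct prescription. Detection is a failure of the measuring tool.

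**What to change.** Reconcile Brief verbal interventions, Allocation and blinding, and Statistical analysis plan with one rule for all four arms:
- **No replacement after the opening request.** From then on every randomised OSP stays in its assigned arm. The opening request is common to all arms, so the rule does not depend on the BVI.
- **Refusal of service** counts as not accurate in the primary ITT analysis and is not imputed. The comparison of served visits, or one using replacement visits, becomes a sensitivity analysis.
- **Detected visits** stay in their arm. Use the prescription obtained, or treat the outcome as missing under the planned multiple imputation, with a sensitivity analysis. Do not score detection itself as failure.
- **Reporting.** Record and report refusals and detections by arm.
- **Replacement** only for OSPs found closed or ineligible before the opening request, taken from a pre-drawn reserve list in the same stratum held by the independent statistician.

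The cost is mainly wording, with fewer replacement visits. If refusals are not rare, the estimated effect and power fall: with 5% refusing in the BVI arm only, the difference is 0.187 and power about 80% instead of 92% under the one-sided formula that reproduces 456. The plan should say so. That smaller difference is the effect once refusals are counted, which replacement would leave out.
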